#### Secondary aims

##### Clinical outcomes

Determine the efficacy of 6–12 months of weekly azithromycin (compared with placebo) on (1) rates and proportion of children with ALRI hospitalisations between treatment groups using negative binomial regression (reporting IRR, 95% CI) while taking the intervention; (2) rates and proportions of children with ALRI hospitalisations between treatment groups using negative binomial regression (reporting IRR, 95% CI) during and post-intervention (at 24 months postcommencement of trial medications); (3) adverse events will be compared between treatment groups using risk differences (95% CI) while on the intervention; and (4) the proportion of children with chronic respiratory symptoms/signs suggestive of underlying CSLD or bronchiectasis at 24 months between treatment groups.

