### Outcomes

The primary outcome is the annualised rate of medically attended ALRIs during the intervention period of 6–12 months when the participants received the trial medications. Outcomes are assessed at 6 and 12 months for those who received 6 and 12 months of study trial medication, respectively.

Secondary outcomes are the rates and proportions of children with:

ALRI hospitalisations during the intervention period at 6–12 months.ALRI hospitalisations during and post-intervention (at 24 months post-commencement of trial medications).Adverse events (eg, nausea, vomiting, diarrhoea and rash).Nasopharyngeal colonisation by macrolide-resistant respiratory pathogens at baseline, (6), 12, 18 and 24 months.Chronic respiratory symptoms/signs suggestive of underlying CSLD or bronchiectasis at 24 months.ICER on the potential benefits (in terms of savings in hospitalisations and medical evacuations, and other associated costs to health services and patients) of azithromycin compared with placebo over the additional costs of administering the drug.

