##### Laboratory outcomes

Determine the efficacy of 6–12 months of weekly azithromycin (compared with placebo) on nasopharyngeal respiratory pathogen carriage and antimicrobial resistance using longitudinal analysis and logistic regression, as done previously.^19^

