##### Sample size

Based on our primary outcome (rate of medically attended ALRI), 80 children per group (total sample size n=160, including 15% attrition) will provide 90% power to detect a 40% reduction (IRR=0.6) in medically attended ALRI episodes per child-year. We assumed a rate of three medically attended ALRI episodes per child-year in the control group, based on community presentations for respiratory illnesses in our setting,^33^ a shape parameter of k=0.4, and a two-sided significance level of 5%. Children who are withdrawn or lost to follow-up (at 6–12 months) will be replaced until the required sample size is obtained. Our previous bronchiectasis RCT^19^ reported a halving of respiratory exacerbations in the azithromycin group and the maximal benefit was achieved between 4 and 14 months of the intervention.^34^

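### The proportion of children hospitalised with an ALRI is assigned to negative binomial regression with an IRR, a count model that does not fit a yes/no outcome and gives intervals that are too wide

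*Protocol article*

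**What the plan says.** The Outcomes section of the protocol article makes rates and proportions two separate summaries: "Secondary outcomes are the rates and proportions of children with" is the stem, and ALRI hospitalisation appears beneath it twice, once for the intervention period and once for the whole period to 24 months.

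Secondary aims (Clinical outcomes) then gives one method for both summaries. Item (1), on treatment, reads "rates and proportion of children with ALRI hospitalisations between treatment groups using negative binomial regression (reporting IRR, 95% CI"). Item (2) repeats it: "rates and proportions of children with ALRI hospitalisations between treatment groups using negative binomial regression (reporting IRR, 95% CI) during and post-intervention". Neither item names a binary method for the proportion, and neither mentions a robust variance.

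Elsewhere the article does name binary methods. In item (3) of the same section, "adverse events will be compared between treatment groups using risk differences (95% CI) while on the intervention". Under Laboratory outcomes, carriage is to be compared together with "antimicrobial resistance using longitudinal analysis and logistic regression, as done previously".

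**The concern.** A negative binomial model describes counts whose variance is at least as large as their mean. Repeated hospitalisations per child can behave like that. Whether a child was ever hospitalised cannot: with probability p, the mean is p and the variance is p(1-p), which is always smaller. The best-fitting dispersion is therefore zero, the edge of its permitted range. What remains at best is a Poisson model, which takes the variance to be p and so overstates it by a factor of 1/(1-p). An incidence rate ratio is also not the natural measure for a proportion; that is a risk ratio or a risk difference.

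Fewer hospitalised episodes is one of the article's secondary hypotheses. If the text is followed literally, the two comparisons of proportions would have confidence intervals wider than the data justify, and would lose power.

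**Working it through.** **The plan's own figure first.** The Sample size section states that "80 children per group (total sample size n=160, including 15% attrition) will provide 90% power to detect a 40% reduction (IRR=0.6"), with 3 episodes per child-year in the control group, k=0.4 and a two-sided 5% level. Taking the variance as mu + k·mu² and one year of follow-up:

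- n per group = (z₀.₉₇₅ + z₀.₉₀)² × [1/3 + 1/1.8 + 2 × 0.4] / (ln 0.6)²
- = (1.960 + 1.282)² × 1.689 / 0.261 = 68.0
- 68/0.85 = 80

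The stated 80 per group is reproduced. It concerns the count outcome and is not affected by this point.

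**Inputs for the proportion.** The article gives no planning value for the proportion hospitalised. Its only anchor, in the Introduction, is that 41 of 162 Northern Territory children (25%) in earlier trials were rehospitalised with a respiratory illness within 6 months. I take 25% as an assumed control risk and show a range of 10% to 50%. A risk ratio of 0.6 is also an assumption, borrowed from the primary outcome. The number per arm is 80.

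**Formulas.** With a and b children hospitalised out of n in each arm, the standard error of the log ratio is:

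- Count model at zero dispersion (Poisson): √(1/a + 1/b)
- Binary model: √(1/a − 1/n + 1/b − 1/n)

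**At 25% v 15% (20 v 12 of 80):**

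- Poisson: √(0.0500 + 0.0833) = 0.365; ratio 0.60, 95% CI 0.29 to 1.23
- Binary: √(0.1333 − 0.0250) = 0.329; ratio 0.60, 95% CI 0.31 to 1.14
- 0.365/0.329 = 1.11, so the count-model standard error is 11% too large

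**Across the assumed range, 80 per arm:**

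| Control risk | Children hospitalised | SE, Poisson | SE, binary | Excess |
|---|---|---|---|---|
| 10% | 8 v 5 | 0.570 | 0.548 | 4% |
| 25% | 20 v 12 | 0.365 | 0.329 | 11% |
| 40% | 32 v 19 | 0.290 | 0.243 | 19% |
| 50% | 40 v 24 | 0.258 | 0.204 | 26% |

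The excess hardly depends on the number per arm: with 68 per arm and 17 v 10 hospitalised, it is again 11%. At 40% control risk the same data give 0.34 to 1.05 under the count model and 0.37 to 0.96 under the binary model, so the choice of model can decide whether the interval excludes 1.

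**Operating characteristics** (simulation, 200,000 draws, 80 per arm; the 50% v 30% line is by exact enumeration):

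- No effect, 25% in both arms: type I error 2.1% under the count model, 4.5% under the binary model
- 25% v 15%: coverage 97.5% v 95.9%; power 26% v 34%
- 40% v 24%: power 41% v 58%
- 50% v 30%: power 51% v 72%

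**Check of the boundary argument.** A negative binomial model fitted in statsmodels to the 20 v 12 data gave an estimated dispersion of 0.00026 and, with its default settings, no standard error. Holding the dispersion at the planning value of 0.4 instead makes the interval wider still (standard error 0.379). A Poisson fit with robust variance returned 0.329, the same as the binary model.

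**The case against.** The strongest reply is that this is compressed wording. An IRR makes sense only for a rate, so the model and the IRR may have been meant for the rates alone, with the proportions carried along from the shared stem in Outcomes. The authors clearly know binary methods, and a detailed SAP is to be approved before the final analysis. This is plausible, and it means nobody can be sure that a negative binomial model will be run on 0/1 data. But it does not remove the point. The text states a method for both quantities, twice, and that method is unsuitable for one of them. This is different from leaving a detail to the SAP.

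The second reply is that the harm is limited. That stands. The intervals err on the wide side, a robust variance would remove the excess (though none is stated), and at a control risk near 10% the effect is trivial.

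Several stronger readings are tempting but not supported:

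- *The model will always fail to fit.* Whether it stops, or returns a near-zero dispersion with or without a standard error, depends on the software and optimiser. It is not a property of the plan.
- *The losses at 40% or 50% control risk are the expected ones.* Longer windows could raise the risk above the 25% anchor, but the article gives no such figure. These scenarios are assumptions.
- *Children treated for 6 and for 12 months make the proportions non-comparable.* The article reports that only 2% have opted out at 6 months, and item (2) has a fixed 24-month window. This is minor.
- *The outcome of chronic symptoms or signs suggesting CSLD or bronchiectasis has the same fault.* Item (4) names no model for it, and that can be left to the SAP.

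**Conclusion.** The point holds as a specification error in two secondary comparisons. As written, the proportion hospitalised is assigned to a model that does not fit it, and to an effect measure meant for rates. At an assumed 25% v 15% with 80 per arm, the cost is a standard error about 11% too large, coverage of about 97.5%, and power of about 26% instead of 34%. The excess ranges from about 4% to about 26% for assumed control risks of 10% to 50%. These figures assume model-based standard errors and a risk ratio of about 0.6.

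A reader might infer that the trial risks false-positive claims, or that its sample size is undermined. Neither follows: type I error falls below its nominal level, the stated 80 per group reproduces, and negative binomial regression remains suitable for the primary outcome and for the hospitalisation rates. Nor does the right model make these comparisons well powered; under the 25% v 15% assumption, power is about 34% even then.

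**What to change.** Split the two quantities in items (1) and (2) of the Clinical outcomes section, and carry the split into the SAP:

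- **Hospitalisation rates:** keep negative binomial regression, reporting the IRR with 95% CI.
- **Proportion of children hospitalised**, during the intervention and to 24 months: use log-binomial regression, or Poisson regression with robust standard errors, reporting the risk ratio and the risk difference with 95% CIs.

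The outcomes and their windows stay as they are in the Outcomes section. If the negative binomial model was always meant for the rates alone, the same sentence settles it. The cost is a line of wording and one extra standard model. The article says the SAP is still to be prepared and approved before the final analysis, so the change can be made there.

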**Methods and analysis:**

We will recruit 160 Australian and New Zealand First Nations and Timorese children aged <2 years to a parallel, superiority RCT across four hospitals from three countries (Australia, New Zealand and Timor-Leste). The primary outcome is the rate of medically attended ALRIs during the intervention period. The secondary outcomes are the rates and proportions of children with ALRI-related hospitalisation, chronic symptoms/signs suggestive of underlying chronic suppurative lung disease or bronchiectasis, serious adverse events, and antimicrobial resistance in the upper airways, and cost-effectiveness analyses.

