## Aims and hypotheses

The primary aim of this RCT is to determine whether 6–12 months of weekly azithromycin (compared with placebo) following hospitalisation for an ALRI reduces the rate of subsequent episodes in First Nations and Timorese children aged <2 years. Our primary hypothesis is that children receiving long-term azithromycin will have fewer medically attended ALRIs over the intervention period than those receiving placebo.

Our secondary aims are to determine the effect of 6–12 months of weekly azithromycin (compared with placebo) on the rates and proportions of participants with ALRI-related hospitalisations, adverse events, nasopharyngeal carriage and antimicrobial resistance of respiratory pathogens and subsequent chronic respiratory symptoms/signs suggestive of underlying CSLD or bronchiectasis at 24 months. We will also assess the cost-effectiveness of the intervention by collecting healthcare-related costs and calculating the incremental cost-effectiveness ratio (ICER) on the potential benefits of azithromycin on hospitalisation, medical evacuations and other associated costs to health services compared with placebo.

Our secondary hypotheses are that 6–12 months of weekly azithromycin will result in reduced hospitalised ALRI episodes and reduced chronic respiratory symptoms/signs suggestive of underlying CSLD or bronchiectasis at 24 months, will be safe and will provide health economic benefits to health services, but with increased antimicrobial resistance in nasopharyngeal respiratory pathogens.

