#### Trial medications

Azithromycin provided as oral powder for suspension (200 mg/5 mL) is administered once per week for 6–12 months. Doses are weight based at 30 mg/kg/week. Equivalent placebo powder for suspension matches the active medication in taste and appearance. The Menzies School of Health Research (Menzies) purchased the trial medications (azithromycin and its corresponding placebo) from the Institute of Drug Technology (Melbourne, Australia), as done previously.^14 19 28^ Trial medications are shipped to sites by trial logistics companies.

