#### Randomisation, allocation concealment and blinding

Randomisation is undertaken by each site’s pharmacy representative who allocates participants to a treatment according to a randomisation sequence. Each site has two randomisation sequences; one stratified by site and the other by whether the child has had a prior ALRI hospitalisation or not. An opaque envelope with the corresponding respective randomisation number is then opened to reveal treatment allocation as one of eight bottle letters (A–H), four allocated to azithromycin and four to placebo. The randomisation sequences were generated by an independent statistician using permuted blocks.

The first dose of trial medication is given in hospital and then dispensed weekly by either a member of the research team, primary health clinic staff or family member (whichever is appropriate) for each site. Adherence is monitored by the research team in weekly medication logs based on parent reports. People masked to the treatment allocation are those (1) receiving the treatment, (2) administering the treatment, (3) assessing the outcomes and (4) analysing the data.

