### Data collection, monitoring and follow-up details

Data are collected by GCP-trained researchers using standardised data collection forms similar to our previous RCTs.^14 15 28^ At enrolment, sociodemographic, clinical and economic data and nasopharyngeal swabs (where possible) are collected (table 1). Sociodemographic details include age, sex, anthropometrics, family and household size, exposure to tobacco smoking (mother and household), breastfeeding, immunisation history, medications (prior to and during hospitalisation), current and previous ALRI history, comorbidities and the eight-item parent-cough specific quality of life (PC-QoL) score.^29 30^ Clinical data include respiratory symptoms/signs, investigations and treatments before and during hospitalisation. These details are obtained either by the parent/guardians and/or review of the child’s medical records.

**Table 1 T1:** Schedule of visits and contact points

		Month					
	Baseline (hospital)	1	4	8*	12*	18	24
Screening for eligibility	√						
Written informed consent	√						
Randomisation	√						
First dose of study medication	√						
Medical history	√						
Medical chart review	√	√	√	√	√	√	√
Clinical assessment _(where possible)_	√	√	√	√	√	√	√
PC-QoL	√	√	√	√	√	√	√
NPS†	√				√	√	√
Semistructured interview							√

* Will instead be done at 6 months for children opting out of the intervention at the 6-month time-point.

† For children living in remote locations in the unlikely event where the research team are physically unable to visit and/or other avenues have been exhausted, specimen collection will not occur in these instances.

NPSnasopharyngeal swabPC-QoLparent-cough quality of life

Medication adherence and adverse events (diarrhoea, vomiting, rash, nausea) logs are maintained either by the parents/guardian or research staff during the intervention period.

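### Adverse events are defined as an outcome by rate and by proportion, but the analysis section names only a risk difference, which ignores repeat events and is the weaker measure if events are common

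*Protocol article*

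**What the plan says.** All references are to the protocol article.

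- **Outcomes** opens its secondary list with "Secondary outcomes are the rates and proportions of children with". Adverse events are an item on that list, with nausea, vomiting, diarrhoea and rash as examples.
- **Aims and hypotheses** uses the same scale: the secondary aims concern the effect of azithromycin "on the rates and proportions of participants with ALRI-related hospitalisations, adverse events" and further outcomes. A secondary hypothesis is that the treatment will be safe.
- **Secondary aims, Clinical outcomes**, item (3), gives the one analysis named for this outcome: "adverse events will be compared between treatment groups using risk differences (95% CI) while on the intervention". Items (1) and (2) of the same sentence give ALRI hospitalisations both rates and proportions, with negative binomial incidence rate ratios.
- **Data collection, monitoring and follow-up details** describes the source: "Medication adherence and adverse events (diarrhoea, vomiting, rash, nausea) logs are maintained either by the parents/guardian or research staff during the intervention period".
- **Trial medications** says that azithromycin "is administered once per week for 6–12 months".
- **Data monitoring, management and analyses** promises a detailed statistical analysis plan, which is not at hand.

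**The concern.** The outcome has two halves and the analysis serves one. Because the neighbouring items do name a rate model, the article is not simply silent on methods at this point. It states an effect measure that does not deliver the outcome as defined, and an analysis plan that follows item (3) would carry the gap forward.

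The missing half could matter in this trial. The children are under 2 years old, the medication runs for up to a year, and the solicited events can recur. A measure based on at least one event scores a child with a single loose stool the same as a child with diarrhoea after many doses. If most placebo children have an event at some time in the year, the difference between arms has little room to show an excess on azithromycin. The safety hypothesis would then be judged on a measure that is weak against the harm most likely to recur.

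**Working it through.** **The plan's own figure.** The Sample size section gives 80 per group including 15% attrition, 90% power, a control rate of 3 per child-year, rate ratio 0.6, k = 0.4 and two-sided 5%. With k as dispersion (variance μ + kμ²) and one year of follow-up:

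n per arm = (1.960 + 1.282)² × (1/3 + 1/1.8 + 2 × 0.4) / (ln 0.6)² = 10.507 × 1.6889 / 0.2609 = 68.0, and 68 / 0.85 = 80.

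The stated size reproduces. It also fixes 68 evaluable children per arm and shows how k is meant. No size or power figure is given for adverse events.

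**Assumptions for adverse events.** The article gives no event frequency, so the placebo rate m is varied from 0.1 to 6 episodes per child-year. The true rate doubles on azithromycin and the window is 12 months. Dispersion 0.4 is borrowed from the ALRI assumption and then varied.

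**Formulas.**

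- Proportion with at least one event: p(m) = 1 − (1 + km)^(−1/k), or 1 − e^(−m) when k = 0.
- Risk difference: power = Φ(RD/SE − 1.96), with SE = √{[p0(1 − p0) + p1(1 − p1)]/68}.
- Rate ratio: power = Φ(ln 2/SE − 1.96), with SE = √{[1/m + 1/(2m) + 2k]/68}.

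**One line in full (m = 1, k = 0.4).** p0 = 1 − 1.4^(−2.5) = 0.569 and p1 = 1 − 1.8^(−2.5) = 0.770, so RD = 0.201. Its SE is 0.0788 and its power 0.723. For the rate ratio, SE = √(2.3/68) = 0.1839, 0.693/0.1839 = 3.77, and power is 0.965.

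**Results with k = 0.4.**

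| Placebo rate per child-year | Ever affected, placebo v azithromycin | Risk difference (points) | Power, risk difference | Power, rate ratio |
|---|---|---|---|---|
| 0.1 | 9% v 17% | 8 | 0.290 | 0.301 |
| 0.25 | 21% v 37% | 15 | 0.520 | 0.592 |
| 0.5 | 37% v 57% | 20 | 0.677 | 0.835 |
| 1 | 57% v 77% | 20 | 0.723 | 0.965 |
| 2 | 77% v 91% | 14 | 0.608 | 0.996 |
| 3 | 86% v 95% | 9 | 0.467 | 0.999 |
| 6 | 95% v 99% | 3.5 | 0.222 | >0.999 |

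A pooled standard error in the test lowers the risk-difference powers by less than 0.02.

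**Other dispersions, at 3 per child-year.**

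- k = 0: 95% v 99.8%, power 0.42 against >0.99.
- k = 1: 75% v 86%, power 0.35 against 0.95.
- k = 2: 62% v 72%, power 0.24 against 0.77.

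Over 0.1 to 6 episodes per child-year and k from 0 to 2, the rate comparison was never the less powerful of the two.

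**The case against.** Several points on the other side are sound.

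- **The rate has not been dropped.** It is a stated outcome in two sections, and the article defers detail to an analysis plan. A reader might infer from item (3) that adverse-event rates will not be analysed; the article does not say so. What stands is that item (3) does name a measure, and that measure covers only the proportion.
- **Saturation is not shown.** A reader might infer that almost every child will have an event and that a doubling will be hidden. The article gives no frequencies. The proportions approach their ceiling only towards the upper part of the assumed range and with limited clustering. At one episode per year the excess is 20 points, which is not hidden.
- **Two premises are inferences.** Weekly logging is stated for medication ("Adherence is monitored by the research team in weekly medication logs based on parent reports"), not explicitly for adverse events. Children ever affected is the natural meaning of a risk difference over the intervention, but those words are not used.
- **Intervals, not a safety test.** The article commits to 95% confidence intervals. At three episodes per year with k = 0.4, the expected interval is 9.2 ± 1.96 × 4.9 points, about −0.4 to 18.9, and a careful reader would not take that as reassurance. The independent committee also monitors all adverse events.
- **Unequal time on medication is minor.** Choice of duration of intervention reports 2% opting out at 6 months to date.
- **A risk difference is a standard, readable measure of harm.** Replacing it as the main measure for every event would be a preference, not a correction.

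These points limit the size of the concern. They do not supply an analysis for the rate.

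**Conclusion.** The point holds as a mismatch between the outcome and its analysis: two sections define adverse events by rates and proportions, and item (3) names a comparison of proportions only. That rests on the text alone.

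The cost in sensitivity is conditional. With 68 per arm, a true doubling, 12 months and dispersion 0.4, the rate comparison has clearly more power from about one placebo episode per child-year (0.965 against 0.723), and the gap widens at three (0.999 against 0.467). For an event as rare as 0.1 per child-year, as rash might be, nothing is lost. The event rates and the dispersion are assumptions.

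The documents do not support the stronger claim that the planned comparison will conceal a doubling of diarrhoea or vomiting. They support saying that it could have little power to show one if these events are common. The primary analysis is not affected.

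**What to change.** In Secondary aims, Clinical outcomes, item (3), and in the analysis plan, add a rate comparison for each solicited event: negative binomial regression with log time on trial medication as offset, or an equivalent repeated-measures model of the logs. Report the rate ratio with its 95% confidence interval alongside the risk difference, and say that the risk difference refers to children with at least one event, if that is meant. The analysis then matches the outcome as defined and follows the form already used for ALRI hospitalisations.

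The cost is one more model per event, plus a rule fixed before unblinding for when consecutive log entries count as one episode and how gaps in the logs are treated. No new data collection is planned for this: the logs are already kept, though the rule should be checked against what they record.
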